## List of Abbreviations

MiPPAD Malaria in Pregnancy Preventive Alternative Drugs

MQf Mefloquine given as full-dose

MQs Mefloquine given as an split dose

AP Analysis Plan

ATP According to protocol

EPI Expanded program for immunization

IPTp Intermittent preventive treatment during pregnancy

IQR Interquartilic range

ITT Intention to treat

LBW Low Birth Weight (<2500g)

LLITNs Long lasting insecticide treated nets

MQ Mefloquine

MUAC Mid-upper arm circumference

RR Risk Ratio

RRate Relative Rate

SP Sulphadoxine-Pyrimethamine

## 1 Introduction

This Analysis Plan (AP) provides detailed description of the descriptive (with the skeleton of the tables) and inferential statistical analysis for the efficacy and safety data collected for mothers in the Trial 1 of the MiPPAD study. Separate APs for children and exploratory analysis are available.

Any planned modification of the analysis should be documented in this AP.

## 2 Trial 1 objectives and endpoints

### 2.1 Primary

1. Prevalence of low birth weight (LBW) newborns (<2500g).

### 2.2 Secondary

1. Peripheral maternal parasitaemia at delivery (microscopic and submicroscopic)
2. Prevalence of *P. falciparum* parasitaemia in cord blood (microscopic and submicroscopic)
3. Prevalence of placental *P. falciparum* infection (histology or blood smear, microscopy and submicroscopic)
4. Mean maternal haemoglobin (g/dL) at delivery
5. Prevalence of maternal anaemia at delivery (< 11g Hb/dL)
6. Prevalence of severe maternal anaemia at delivery (< 7g Hb/dL)
7. Prevalence of neonatal anemia (Hb<12.5 g/dL in case of cord blood, or Hb <13 g/dL in case of peripheral blood )
8. Mean birth weight (in grams)
9. Prevalence of prematurity
10. Number of stillbirths
11. Number of miscarriages
12. Frequency of congenital malformations.
13. Mean gestational age at birth (assessed by Ballard score in the newborn)
14. Incidence of vomiting
15. Incidence of dizziness
16. Frequency of drug adverse reactions
17. Incidence of clinical malaria during pregnancy
18. Incidence of overall maternal admissions/outpatient attendances
19. Neonatal and infant mortality rate

---

Only in a subsample of participants

20. Incidence of clinical malaria in the first year of life
21. Peripheral maternal parasitaemia 1 month after end of pregnancy (microscopic and submicroscopic)

### 2.3 Exploratory

1. Frequency of congenital malaria
2. Prevalence of Malaria, development and physicomotor development of children
3. Safety (SAEs) in children
4. Pharmacovigilance (to be presented in a separate document)
5. ... *Exploratory endpoints (to be completed)*

## 3 Study design overview

This is a randomized open-label superiority 3 arms trial to compare 2-dose MQ with two dose of SP as IPTp in the prevention of the adverse effects of malaria during pregnancy and to compare MQ tolerability of 2 different MQ administration regimens. The three arms of the study are:

1. IPTp with SP (SP)
2. IPTp with MQ given as full dose (MQf)
3. IPTp with MQ given as an split dose (MQs)

The table 1 shows the visits and procedures schedules to the mother and the table 2 shows the visits and procedures schedule to the child.

---

At visit 4, approximately one month after end of pregnancy

Table 1: Maternal visits and procedures schedule

| Study Procedures                                    | Visit 1
Enrollment | Visit 2 | Visit 3
Delivery | Visit 4
1 Month | Unscheduled
visits | Household
visits |
|-----------------------------------------------------|-----------------------|---------|---------------------|--------------------|-----------------------|---------------------|
| Inclusion/Exclusion criteria                        | X                     |         |                     |                    |                       |                     |
| Written informed consent                            | X                     |         |                     |                    |                       |                     |
| Demographics/Medical history                        | X                     |         |                     |                    |                       |                     |
| Record of concomitant medication/
Adverse events | X                     | X       | X                   | X                  | X                     |                     |
| Physical examination / Clinical                     | X                     |         |                     |                    | X                     |                     |
| Gestational Age                                     | X                     | X       | X                   |                    | X                     |                     |
| Temperature                                         |                       |         |                     | X                  | X                     |                     |
| Blood Pressure                                      |                       |         | X                   |                    | X                     |                     |

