## 5 Statistical methods

For the primary analysis of efficacy, the statistical analysis will follow a sequential approach. First, hypotheses of non-inferiority between the proportion of LBW in the MQ groups and the SP group will be tested assuming as equivalence a 25% reduction or greater in LBW prevalence in the MQ groups. If non-inferiority between MQ and SP is achieved, then an analysis for superiority will be conducted comparing the MQ and SP groups using a two-sided test. Given the long half life of MQ, it has been assumed that MQ efficacy to prevent LBW will be equal in the full dose and split dose groups.

Interpretation of non-inferiority is based on the confidence intervals (CI). If the upper limit of the confidence interval (CI) of the Relative Risk (RR) MQ/SP is below 1.25, (25% of the RR) the MQ arms will be considered as non-inferior compared with SP (See figure 1). In case the upper limit of the CI is above 1.25, the trial is inconclusive as the non-inferiority hypothesis can't be rejected. If both the lower limit of the CI is below 1, the MQ treatment is considered superior to SP (See figure 2).

[figure not shown]

Figure 1: Rules for Non-inferiority

No adjustment of p-values are necessary to this switch as the “delta“ has been pre-specified, and then the interpretation based on confidence intervals can support the interpretation of non-inferiority. It is acceptable to calculate the p-value associated with a superiority test and to evaluate whether this is sufficiently small to reject convincingly the hypothesis of no difference. There is no multiplicity that affect this interpretation because in statistical terms it corresponds to a simple closed test procedure (Committee for Proprietary Medicinal Products CPMP, Points to consider on switching between superiority and non-inferiority, CMP/EWP/482/99, July 2000).

Proportions will be compared between groups using fisher exact test and presented as Risk ratio (RR) or reduction of the RR ( $1 - RR * 100\%$ ) if RR lower than 1. Adjustment for covariates and possible confounder are done using binomial regression with log link, and using robust estimates of the covariance (huber method) using the method proposed by Zou (Zou G., A modified poisson regression approach to prospective studies with binary data. American Journal of Epidemiology. 2004;159(7):702-706).

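### Section 3 labels the trial superiority while section 5 tests non-inferiority first, and the printed superiority rule cannot separate a non-inferior-only result from a superior one

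*SAP*

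**What the plan says.** - **Section 3 (Study design overview)** gives the design in one sentence: "This is a randomized open-label superiority 3 arms trial to compare 2-dose MQ with two dose of SP as IPTp". It does not mention non-inferiority and sets no decision rule.
- **Section 2.1** names the primary endpoint, LBW prevalence, without a hypothesis.
- **Section 5 (Statistical methods)** sets the order of the primary tests: "First, hypotheses of non-inferiority between the proportion of LBW in the MQ groups and the SP group will be tested". The second step is conditional: "If non-inferiority between MQ and SP is achieved, then an analysis for superiority will be conducted". That second test is to be two-sided.
- **Non-inferiority rule (section 5).** If the upper limit for RR MQ/SP "is below 1.25, (25% of the RR) the MQ arms will be considered as non-inferior compared with SP". If the margin is missed: "In case the upper limit of the CI is above 1.25, the trial is inconclusive".
- **Superiority rule (section 5).** The next sentence calls MQ superior when the lower confidence limit lies under 1. It contains a stray "both" with only one limit named, which suggests that words are missing. It points to Figure 2, which is not reproduced in the text at hand.
- **Opening sentence of section 5.** It describes the margin as "assuming as equivalence a 25% reduction or greater in LBW prevalence in the MQ groups", which runs in the opposite direction from an upper limit of 1.25.

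**The concern.** A reader of section 3 expects the primary objective to be met only if MQ lowers LBW prevalence relative to SP. A reader of section 5 sees non-inferiority tested first, labelled as a conclusion in its own right, and used to decide whether the trial is inconclusive. Nothing in the SAP reconciles the two.

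The case that matters is an upper limit between 1 and 1.25. If superiority is the objective, it has not been shown. If non-inferiority is the objective, it has been met. A closed procedure allows both tests but does not say which one answers the trial's question. The superiority sentence should mark the boundary between these results, and as printed it does not, because the limit it names is the wrong one for an adverse outcome. At stake is whether the report says that MQ is better than SP or only that it is not worse by more than the margin.

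**Working it through.** The SAP states no power, sample size or expected LBW rate, so there is no figure of its own to reproduce. The check has two parts.

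**1. The printed rules applied to one interval.** LBW is an adverse outcome and the ratio is MQ/SP, so values below 1 favour MQ. Take an RR interval of 0.88 to 1.20.

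- Non-inferiority: 1.20 < 1.25, met.
- Superiority as printed: the lower limit 0.88 < 1, so MQ is called superior.
- Superiority by the two-sided test that section 5 also specifies: the interval contains 1, so superiority is not shown at the matching level.

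The text therefore gives two answers on superiority for the same data.

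**2. When the printed rule adds nothing to non-inferiority.** If the ratio of upper to lower limit is above 1.25, an upper limit below 1.25 forces the lower limit below 1, because lower = upper / ratio < 1.25 / 1.25 = 1. Every non-inferior result would then also be called superior.

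Assumptions, for illustration only: pooled MQ to SP 2:1, SP arm n from 500 to 2000, LBW prevalence p from 8% to 16%, true RR = 1, 95% interval (the level in Table 9), normal approximation on log RR.

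- SE = sqrt((1−p)/(2np) + (1−p)/(np)) = sqrt(1.5(1−p)/(np))
- Ratio of limits = exp(2 × 1.96 × SE)
- P(upper < 1.25) = Φ(ln 1.25/SE − 1.96), with ln 1.25 = 0.2231
- P(upper < 1) = Φ(−1.96) = 2.5%

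| SP n | LBW | SE | Ratio of limits | P(upper < 1.25) | P(upper < 1) |
|---|---|---|---|---|---|
| 500 | 8% | sqrt(1.38/40) = 0.186 | 2.07 | 22.4% | 2.5% |
| 1500 | 13% | sqrt(1.305/195) = 0.082 | 1.38 | 77.9% | 2.5% |
| 2000 | 16% | sqrt(1.26/320) = 0.063 | 1.28 | 94.5% | 2.5% |

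The ratio exceeds 1.25 even in the most precise case (1.28). Throughout this range, then, the printed sentence read alone would turn every non-inferior result into a superior one. In the middle case an observed RR of 1.00 has an interval of exp(±1.96 × 0.0818) = 0.85 to 1.17: non-inferior, superior as printed, and not superior by a two-sided test.

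With true RR = 1, the chance of an upper limit from 1 to below 1.25 is the difference of the last two columns: 19.9% (22.4 − 2.5) to 92.0% (94.5 − 2.5). This shows only that the unresolved band can be a common outcome.

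**The case against.** The strongest defence is that section 3 is a one-sentence overview and section 5 alone decides the primary endpoint. Order, margin and gate are fixed there, with a closed-test argument. At the same confidence level and in the same population, an upper limit below 1 implies one below 1.25, so the gate costs superiority neither alpha nor power. Section 5 does label a result inside the margin as non-inferior. The primary objective may be stated in the protocol, which is not at hand, and Figure 2 may draw the superiority rule correctly.

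Most of this stands, and it rules out several stronger readings:

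- A reader might infer that MQ performing like SP is a failure under section 3 and a success under section 5. Section 3 sets no success rule, section 5 says non-inferior rather than success, and a result near 1 is non-inferior only if the interval is narrow enough.
- A reader might infer that either headline could be picked after the data are seen. The pre-specified sequence limits that: non-inferior with superiority not shown is a single, consistent result.
- A reader might infer type I error inflation from the switch. The closed sequence causes none.
- A reader might take the percentages above as the effect of the word superiority in section 3. They are not: the section 5 analysis is the same whichever label is used, and passing 1.25 is easier than excluding 1 in any such design.

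The defence does not remove two points. The two SAP sections disagree with each other whatever the protocol says. And the closed-test argument presupposes a correct superiority criterion, which the printed sentence does not supply.

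**Conclusion.** The concern holds in a limited form. The SAP names superiority as the design and tests non-inferiority first, without saying which conclusion meets the primary objective. As printed, its text cannot separate non-inferior only from superior, and would call 0.88 to 1.20 superior.

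The part about the label rests on the text alone. The part about the rule rests on a literal reading of one sentence that appears to have lost words. It would be unsafe to infer that the analysis will in fact declare superiority wrongly, since section 5 also requires a two-sided test and Figure 2 may differ. The probabilities depend on assumed sample size, LBW rate and 2:1 pooling, and serve only to show that the affected band is not rare. This should be corrected before analysis; it does not undermine the sequential design itself.

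**What to change.** 1. **Section 3.** Describe the trial as randomized, open-label, with three arms, testing non-inferiority of MQ to SP on LBW (margin RR 1.25) and then superiority if non-inferiority is met. If superiority is the primary objective, keep the label and state in section 5 that non-inferiority alone does not meet that objective.
2. **Section 5.** Replace the superiority sentence with three bands for the upper limit of RR MQ/SP:
   - below 1: MQ superior;
   - from 1 to below 1.25: MQ non-inferior, superiority not shown;
   - 1.25 or above: non-inferiority not shown.
3. **Consistency.** Check Figures 1 and 2 against these bands, and reword the opening sentence of section 5 so that the margin runs in the same direction as the 1.25 rule.

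The cost is wording only. No data, sample size or analysis changes. The sponsor commits in writing, before the analysis, to which conclusion meets the primary objective.

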
Table 2: Infants visits and procedures schedule

| Study Procedure                   | At Birth | 1 month§ | 9 months* | 12 months* | Unscheduled visits |
|-----------------------------------|----------|----------|-----------|------------|--------------------|
| Medical history                   | X        | X        | X         |            | X                  |
| Physical examination              | X        | X        | X         | X          | X                  |
| Psychomotor development assesment | X        | X        | X         | X          |                    |
| MUAC                              |          | X        | X         | X          | X                  |
| Weight                            | X        | X        | X         | X          |                    |
| Height                            | X        | X        | X         | X          |                    |
| Temperature                       | X        | X        | X         | X          |                    |
| Blood smear                       | X        | †        | †         | †          |                    |
| Haemoglobin test                  | X        | †        | †         | †          |                    |

\* Household visits in case they do not attend the scheduled visits at study health facilities.

†Only if fever ( $\geq 37.5^{\circ}\text{C}$ ) or history of fever in the past 24 hours or signs suggestive of malaria.

§First visit will be scheduled 1 month after birth or coinciding with first EPI visit

## 4 Population of analysis

### 4.1 According to protocol (ATP)

This population includes all women who fulfill all the inclusion-exclusion criteria and took the two IPTp doses, received the LLITNs and from whom data is available for the analysis.

It will be excluded from the ATP analysis if :

- No fulfill inclusion criteria
- No data on outcome
- No two complete doses of IPTp
- Only half dose of MQs
- More than 48 hours for second dose of MQs
- Less than 4 weeks (28 days) between doses of IPT (for MQs between first half dose)
- Less tablets than specified in the protocol
- Wrong study drug medication
- Weight recorded more than 7 days after delivery
- Do not receive LLITN
- Delivery of twins
- HIV infection in pregnancy

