Continuous variables will be compared between groups and adjusted for covariates and possible confounders using ordinary least square regression. Variables will be transformed to the logarithm scale if normality is improved and result presented as Proportional Difference.

Incidence of clinical malaria, overall admissions and outpatient attendances will be estimated as the number of episodes over the time at risk. Time at risk is estimated as the time from the start of follow up (recruitment in mothers, day of birth in infants) until the end of follow-up (visit one month after

[figure not shown]

Figure 2: Rules for Superiority

delivery for mothers and visit after 12 months of age in infants) or withdrawal due to censoring or death, whatever occurs first. In order to avoid to count twice the same episode of clinical malaria, subjects will not contribute to the denominator nor the numerator during an arbitrary period of 28 days after an event of clinical malaria is defined. For admissions and outpatient attendances a maximum of one episode per day will be allowed. The total number of events will be compared between groups using negative binomial regression to take into account a possible extra Poisson variation due to different frailty of the subjects. The comparison will be expressed as Relative Rate (RRate)

For the ATP cohorts, in order to allow for center differences, regression models will include site as covariate as well as season. The definition of season will be independent for each site. Interaction between site and treatment to evaluate homogeneity will be estimated using a combined test for the interaction terms. In addition of the adjusted results, the crude results for ATP cohort will be also presented.

For the efficacy, analysis will be presented for ATP and ITT populations. The analysis of ITT population are not adjusted for possible confounders. For Safety and Tolerability, analysis will be presented for Safety and ITT populations, all of them unadjusted. See section 6 for the classification of endpoints efficacy, safety or tolerability.

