For the ITT analysis of primary endpoint, which includes all women recruited in the study, missing values for low birth weight will be imputed as follow: For those women with miscarriage, the event will be considered as failure and they will be assigned as having LBW. For those lost to follow-up or withdraw before delivery a sensitivity analysis of worse case scenario assuming all lost of follow-up and withdrawn women having a LBW, best case scenario assuming that none have LBW and worst case scenario assuming as LBW all missing values, will be presented. In case there were countries without malaria events, a sensitivity analysis not including those countries will be also presented.

The assumption that  $MQ_s$  and  $MQ_f$  have a similar effect on the LBW will be explored by inspection of the 90% confidence intervals of the comparison between  $MQ_s$  vs  $MQ_f$  in the ATP population. If the assumption of both MQ groups are similar is rejected, then comparison between  $MQ_s$  vs SP and  $MQ_f$  vs SP will be presented instead.

For the primary outcome, the weight of children born taken after delivery but before the seven days of life are transformed according to the method proposed by ... *Greenwod* (*to be completed*) to include in

A regression analysis of the weight and day after delivery

the analysis as if they were taken at birth. Maternal and new born haemoglobines from visit 3(Delivery) not taken in the date of the delivery will not be included in the analysis of these outcomes.

The gestational age will be based on the Ballard score, but in case of missing, it will be based on the gestational age calculated with the fundal height at recruitment.

For the frequency of vomiting, dizziness, prematurity, the proportion of women with those outcomes will be compared using the methods described for proportions before.

For the tolerability, only those vomiting and dizziness judged by the investigators to be related to the medication will be included in the analysis except vomiting during the first 60 minutes after a dose of IPTp that will always be considered related to medication.

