## 6.3 Efficacy (ATP Adjusted, ATP crude, ITT)

Efficacy endpoints refers to the effect of MQ on the low birth weight, different forms of malaria infection, malaria disease and anaemia. Analysis are presented adjusted for ATP and also crude for ATP and ITT populations. For the primary endpoint, the sensitivity analysis using best, worst and maximum bias scenarios will be presented. Secondary endpoints will be presented crude for ITT population, and adjusted for country in ATP population. If interaction between country and treatment is significant, secondary endpoints will be also presented by country.

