†Submicroscopic infection determined only in a subsample.

Table 13: Secondary endpoints (continous variables)

| Variable                                 | Group    | N            | mean           | sd                          | Diff (95% CI)     | p-value |
|------------------------------------------|----------|--------------|----------------|-----------------------------|-------------------|---------|
| Maternal Hemoglobin (g/dL) when.. | MQ
SP | ####
#### | ##.##
##.## | ##.##
##.##              | #.## (#.##; #.##) | #####   |
| Variable                                 | Group    | N            | Geometric mean | IQR                         | PDiff (95% CI)    | p-value |
| Gestational age (weeks) when..    | MQ
SP | ####
#### | ##.##
##.## | ##.##:##.##
##.##: ##.## | #.## (#.##; #.##) | #####   |

Diff = difference between groups. PDiff= Proportional difference between group. IRQ: Interquartilic range

Table 14: Secondary endpoints (incidence)

| Variable                                       | Group | N    | Events | PYAR | Incidence | RRate (95% CI)    | p-value |
|------------------------------------------------|-------|------|--------|------|-----------|-------------------|---------|
| Clinical malaria during pregnancy              | MQ    | #### | ##     | #### | #.####    | #.## (#.##; #.##) | #.####  |
|                                                | SP    | #### | ##     | #### | #.####    |                   |         |
| Overall number of maternal hospital admissions | MQ    | #### | ##     | #### | #.####    | #.## (#.##; #.##) | #.####  |
|                                                | SP    | #### | ##     | #### | #.####    |                   |         |
| Outpatient number of maternal visits           | MQ    | #### | ##     | #### | #.####    | #.## (#.##; #.##) | #.####  |
|                                                | SP    | #### | ##     | #### | #.####    |                   |         |

RRatio: Relative Ratio, N: Number of subject per group, PYAR: Person years at risk.

Table 15: Secondary endpoints (endpoints for neonatal mortality)

| Variable                 | Group | N    | n(%)      | RR (95% CI)       | p-value |
|--------------------------|-------|------|-----------|-------------------|---------|
| Perinatal mortality      | MQ    | #### | ## (##.%) | #.## (#.##; #.##) | #.####  |
|                          | SP    | #### | ## (##.%) |                   |         |

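### A timing rule that matters only for birth weight is written as a general ATP exclusion, so compliant women with valid malaria or anaemia data leave the only adjusted secondary analyses

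*SAP*

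**What the plan says.** Section 4.1 introduces its list of ATP exclusions with "It will be excluded from the ATP analysis if". Most items concern eligibility, dosing, dose intervals, study drug or net provision. The list also contains "Weight recorded more than 7 days after delivery" and "Delivery of twins". No item is tied to a particular endpoint, and no second ATP set is defined.

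Section 5 then states "For the efficacy, analysis will be presented for ATP and ITT populations". Section 6.3 sets the scope: "Efficacy endpoints refers to the effect of MQ on the low birth weight, different forms of malaria infection, malaria disease and anaemia". For the secondary endpoints it adds "Secondary endpoints will be presented crude for ITT population, and adjusted for country in ATP population". Table 12 lists maternal, placental and cord infection and anaemia, and Table 14 lists "Clinical malaria during pregnancy".

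Section 5 mentions the seven-day limit a second time, and there restricts it: "For the primary outcome, the weight of children born taken after delivery but before the seven days of life are transformed". The same part of section 5 deals with delivery haemoglobins taken on another day by leaving them out of the haemoglobin outcomes alone.

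Section 4.2 makes ITT the target efficacy population. It includes all randomised women and has none of these exclusions.

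**The concern.** An ATP analysis is meant to describe women who were eligible and took the preventive treatment as planned. A late weighing says nothing about either. It affects only whether the recorded weight can stand for birth weight. Placed in the general list, the rule removes the woman from every ATP efficacy analysis, including those for which her data are complete.

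Take a woman who took both doses on time and received her net, whose baby was first weighed on day 9, and who attended the one-month visit. Her clinical malaria history and her one-month smear are valid. Followed literally, section 4.1 drops her from the ATP analysis of both.

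What is at stake is precision in the ATP secondary results. Section 5 leaves the ITT analyses unadjusted, so the ATP results are the only adjusted estimates for these endpoints.

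**Working it through.** The point is mainly textual. The SAP offers no figure to reproduce.

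**1. Is the exclusion conditional?** No. In section 4.1 it is a separate item under a heading that refers to the ATP analysis as a whole.

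**2. Is that population used beyond birth weight?** Yes. Sections 5 and 6.3 apply it to malaria infection, malaria disease and anaemia. Admissions and outpatient attendances also appear in Table 14, but section 6.3 does not name them in its definition of efficacy. They are affected only if their place in that table makes them ATP endpoints.

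**3. Does the SAP treat timing problems this way elsewhere?** No.

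| Timing problem | Where | What is removed |
|---|---|---|
| Weight taken after delivery but within the first week | Section 5 | Nothing; the value is transformed, for the primary outcome |
| Haemoglobin not taken on the delivery date | Section 5 | The woman or newborn, from the haemoglobin outcomes only |
| Weight taken after day 7 | Section 4.1 | The woman, from every ATP analysis |

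The third row is out of line with the other two.

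**4. Which endpoints lose data?** Those for which the woman still has a valid value. Clinical malaria in pregnancy and one-month parasitaemia do not depend on delivery-day sampling, so they are the clearest cases. For delivery endpoints, such as maternal anaemia, the loss depends on whether women with late weights were sampled at delivery, which the SAP does not say.

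**5. How large is the loss?** The SAP gives no rate of late weights, so this is an illustration under an assumption. Let f be the share of otherwise eligible women with a late weight. With interval width proportional to 1/√n, the widening factor is 1/√(1 − f).

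- f = 0.02: 1/√0.98 = 1.010, about 1% wider.
- f = 0.10: 1/√0.90 = 1.054, about 5% wider.

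The range of 2% to 10% is assumed, not taken from the document.

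**The case against.** The strongest reply is that an endpoint-by-endpoint reading was intended. Section 4.1 asks that data be available for the analysis and excludes women without outcome data, and both conditions depend on which analysis is being run. Section 5 also speaks once of ATP cohorts in the plural. On that reading, a late weight just means that there is no usable birth weight. The intent is plausible, but the text does not deliver it: the late-weight item stands on its own, applies even when the endpoint's data exist, and no second cohort is defined. If this was the intent, the correction only records it.

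A second reply is that one fixed ATP set keeps the same women across the profile, baseline and efficacy tables. That has some value. However, the missing-outcome criterion, if judged per endpoint, already lets the ATP number differ between tables.

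Third, the consequence is small, because ITT is the target population and crude ITT estimates remain valid in a randomised trial. This stands, and it limits the point.

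A reader might go further and infer three things that the SAP does not support:

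- *That the treatment comparison is biased.* Nothing suggests that late weighing differs by arm. A link between late weighing and delivery away from a facility is plausible but is not in the SAP. ATP already selects on post-randomisation events such as completing both doses.
- *That valid malaria data are lost to the trial.* They remain in the ITT analysis.
- *That the twin exclusion is misplaced in the same way.* Twins bear on gestational age and prematurity as well as birth weight. They also raise a unit-of-analysis question for cord, placental, neonatal and mortality endpoints, where the tables count one subject but a twin mother may contribute two infants. A singleton ATP set avoids that question and is defensible.

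**Conclusion.** The point holds for the late-weight exclusion. As written, section 4.1 removes compliant women with valid malaria, parasitaemia or anaemia data from the ATP analyses of those endpoints, for a reason relevant only to birth weight and against the SAP's own outcome-specific handling of timing in section 5.

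The impact is limited to some lost precision in ATP. Its size cannot be established from the SAP; the 1% to 5% widening rests wholly on the assumed 2% to 10% of late weights. The ITT analysis is unaffected. The correction is worth making because it is specific and nearly free, not because a main conclusion depends on it.

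**What to change.** In section 4.1:

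1. Move the late-weight item out of the general list and apply it only to low birth weight and mean birth weight.
2. State that missing outcome data are judged separately for each endpoint.
3. Keep the twin exclusion for birth-size, gestational-age, prematurity, cord, placental, neonatal and mortality endpoints, and say so. Lifting it for purely maternal endpoints counted once per woman, such as clinical malaria and maternal peripheral parasitaemia, is optional. It should not be lifted for infant, cord or placental endpoints without a rule for which twin counts and how clustering is handled.

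The cost is a few lines of wording, one extra population flag in the analysis dataset, and a footnote that the ATP number differs between tables. The profile and baseline tables should say which ATP set they describe. No new data are needed.
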